**Fig. 7 Fig7:**
[figure not shown]
Example of stereotactic biopsy within a habitat of the posterior thigh. (**A**) MRI identification of Habitat 1 (blue) target. To account for sofit tissue rotation, needle insertion is designated at the proximal tattoo (BB#1) and a depth of 7 cm towards the center of the femur is measured, with a medial tangential 5.5 cm line (90 degrees), creating the final biopsy track 9 cm from the surface. (**B**) CT measurements, biopsy, and clip placement are illustrated. Each site is defined by a different marker (e.g., one visicoil proximal biopsy, two visicoils at midpoint habitat, and one visicoil plus one helical mammotome for the distal habitat sampled). In addition to helping with daily set up, these markers will also be used at the time of pathological evaluation to orient the specimen and determine treatment response within each habitat

### Adverse event assessment

Adverse event (AE) and serious AE (SAE) assessment will occur during weekly OTVs, post-RT follow-up (between one to three weeks after completion of RT), and up to four months (< 120 days) after surgery. Grading of AEs will be documented based on Common Terminology Criteria for Adverse Events (CTCAE) v5.0. SAEs will be those that result in death, a life-threatening AE, inpatient hospitalization (> 24 h) or prolongation of existing hospitalization, a persistent or significant incapacity or substantial disruption of the ability to conduct normal life functions. In addition to the assessment of all AEs by CTCAE, surgery AEs are explicitly asked for and collected in detail, including peri-operative and postoperative complications. Major wound complication is defined as a wound that requires more surgery, an invasive procedure (e.g., aspiration), and readmission for wound care and/or IV antibiotic use within 120 days after surgery. In addition, any deep packing (packing to dermis in an area of a dehisced wound measuring 2 cm in length) that is needed for over 120 days will also be included as a major wound complication. Although we are not powered to interpret the long-term sequela, we will continue to follow patients off-trial and beyond 4 months postop, as per NCCN guidelines [42]. The range of two to fourth months postoperative follow up in the trial schema is to account for patients that have evaluation prior to four months and are fully healed, but those patients who have post-operative complications will continue on the trial until four months.

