#### Secondary endpoints

Margin status estimate as defined as the final tumor margin of the surgical specimen will be conducted by pathologist. A clear margin (R0) or a positive margin (R1/R2) will be designated, along with the location of the margin, which will be radiographically correlated to the habitat.Pathologic response of each habitat delineated on pathology specimen as determined by the difference in tumor response by various heterogenous portions of the tumor, as delineated by MRI-directed pre-RT clip placement.Rate and types of adverse events evaluated during weekly on-treatment visits (OTVs) up to 4 months (< 120 days) post-surgery.Disease control, determined as the absence of local tumor progression, to be per assessment of the treating radiation oncologist (i.e., clinical assessment) and radiologist (i.e., radiological assessment) for up to 4 months after surgery.Survival, as assessed by clinical visit, virtual visit, or telephone visit for up to 4 months after surgery.

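### The deep-packing component of major wound complication cannot be met within the on-trial adverse-event window; the other components need an explicit connector and equal follow-up for every operated patient

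*Protocol article*

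**What the plan says.** The Adverse event assessment section of the protocol article defines major wound complication in two sentences. The first covers "a wound that requires more surgery, an invasive procedure (e.g., aspiration), and readmission for wound care and/or IV antibiotic use within 120 days after surgery". The second adds deep packing of a dehisced area "that is needed for over 120 days will also be included as a major wound complication".

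The same section places adverse-event assessment at weekly treatment visits, at a visit after radiotherapy, "and up to four months (< 120 days) after surgery". The Secondary endpoints section gives the same limit: "Rate and types of adverse events evaluated during weekly on-treatment visits (OTVs) up to 4 months (< 120 days) post-surgery".

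The section also explains why the schema shows a final visit at two to four months. The range is meant "to account for patients that have evaluation prior to four months and are fully healed", while patients with complications remain on trial until four months. Follow-up beyond four months continues off trial. The Data analysis section tabulates acute wound complications after surgery by type and grade.

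**The concern.** Three features of the definition and its follow-up do not fit together.

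- **Packing.** The duration that makes packing a major complication is longer than the period in which adverse events are assessed on trial.
- **Connectors.** The other items form a list whose connectors allow two readings. On one, any single item makes a case. On the other, several items must occur together.
- **Follow-up.** The definition refers to 120 days, but on-trial follow-up may stop from two months in patients who have healed. The length of observation then depends on how the wound has done so far.

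Safety of the escalated dose is a secondary objective, and the Background and Discussion sections both expect escalation to add little toxicity. In a single-arm trial, readers will set the wound complication rate against outside experience. They can do that only if they know what counts as a case and for how long each patient was observed.

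**Working it through.** The article states no wound complication rate, so there is no figure to reproduce. The check is a day count with surgery as day 0.

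**Packing against the window**

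Inputs, from Adverse event assessment and Secondary endpoints: the window is less than 120 days, so its last day is 119. The required packing duration is over 120 days, so at least 121 full days. The latest possible start of packing is the last day of the window minus 121.

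| Reading of the window | Last day | Latest start of packing |
|---|---|---|
| Less than 120 days, as written | 119 | 119 − 121 = day −2 |
| Four calendar months, shortest | 120 | 120 − 121 = day −1 |
| Four calendar months, longest | 123 | 123 − 121 = day 2 |

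Under the written window, packing would have to begin before the operation. Under the most generous calendar reading it would have to begin by day 2. If the 120 days of packing are instead counted from surgery, the need would have to be seen on day 121 or later, which is still beyond day 119.

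**The other items against the window**

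These are timed within 120 days after surgery. They fit a window ending on day 119, apart from day 120 itself, so they are observable.

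**Connectors**

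The list runs: more surgery, an invasive procedure, *and* readmission for wound care *and/or* IV antibiotics. Take a patient whose only event is a re-operation. If the items are alternatives, that patient is a case. If *and* is read strictly, the patient is not. The next sentence brings in packing as a clear addition, but nothing equally clear separates the items in the first sentence.

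**Early release**

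Two calendar months is 59 to 62 days. For a patient released as healed at that point, the part of the 120-day window without on-trial assessment is:

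- 120 − 62 = 58 days, and 58/120 = 48%
- 120 − 59 = 61 days, and 61/120 = 51%

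This is the extreme case. A later release leaves less unobserved, and the article does not say how many patients will leave early.

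**Scale of one event (illustration only)**

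One missed event changes a rate by 1/36 = 2.8 percentage points with 36 patients, by 1/23 = 4.3 with 23, and by 1/43 = 2.3 with 43. The 36 and 23 are counts evaluable for pathologic response, and 43 is planned enrolment. None is the number of operated patients, and none of these figures estimates how many events would be missed.

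**The case against.** The best defence is that the safety information is collected whatever the label. The article says that surgical adverse events are asked for explicitly and recorded in detail, grades all adverse events by CTCAE, and tabulates wound complications by type and grade. A re-operation or prolonged dehiscence on trial would appear in those tables. Major wound complication is a defined event under the secondary adverse-event endpoint. It is not a listed endpoint, and no test or decision rule in the article uses it. The article also condenses a full protocol that is not shown. All of this stands, and it limits the weight of the point. It does not remove the conflict between two durations that the article itself states.

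Off-trial follow-up might seem to rescue the packing component. It does not, because the article states no adverse-event collection for that period.

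A reader might infer more than the text supports:

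- **That major wound complication as a whole cannot be observed.** Only packing conflicts with the window. Early release does not cause that conflict, since it applies to healed patients and those with complications stay to four months.
- **That a re-operation alone will not count.** The sentence can be read naturally as a list of qualifying events. The fault is ambiguity, not a fixed rule.
- **That every feature is shown to lower the reported rate.** The connector does so only on its strict reading. Early release does so only if healed patients have later events that go unrecorded.

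**Conclusion.** The point holds for one component, one ambiguity and one gap in ascertainment.

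- **Component.** Deep packing of the stated duration cannot be met within the stated on-trial window, so it would contribute essentially no events. This follows from the article's own day limits and needs no outside assumption. Reading four months as calendar months barely alters it.
- **Ambiguity.** The text does not settle whether one of the remaining items is sufficient, and the two readings can give different rates.
- **Gap.** Observation time depends on outcome. For release at two months, about half of the 120-day window has no on-trial assessment. The number of events missed is unknown. Any shortfall assumes that some patients released as healed have a qualifying event later and that it is not recorded on trial.

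The matter should be corrected because it affects how a safety rate is read. It does not touch the primary endpoint, the sample size or the power.

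**What to change.** Four changes:

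1. Reconcile the packing duration with the adverse-event window in Adverse event assessment and Secondary endpoints, so that the component can be observed on trial. Which of the two should move is for the sponsor. Settle at the same time whether day 120 lies inside the window.
2. State the connectors explicitly, so that it is clear whether any one item suffices.
3. Give every operated patient the same ascertainment period, through a contact at the end of the 120-day window whether or not the wound has healed. A telephone call suffices, and the article already accepts that mode for another endpoint: "Survival, as assessed by clinical visit, virtual visit, or telephone visit for up to 4 months after surgery".
4. Report the major wound complication rate over all operated patients.

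The cost is a change of wording and one extra call for each patient who heals early. The reported rate may be higher than under the present text.

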### Statistical considerations

#### Sample size and interim analyses

The primary endpoint is evaluating the FPR rate of patients with resectable non-metastatic high-grade STS treated to GARD-optimized RT dose utilizing MRI habitat–directed neoadjuvant radiation therapy. GARD-based modeling predicted that increasing the dose (60 to 70 Gy) would triple the FPR to an average of > 24.3%. The null hypothesis that the true FPR is 7.9%, which will be tested against a 1-sided alternative hypothesis that the FPR is 24%. We determined the sample size of a maximum of 43 patients using Fleming’s three-stage optimal design, which has a one-sided significance level of 5% and a power of 81.8% if the true FPR is 24% under the alternative hypothesis. The trial is carried out in 3 stages. In the first stage, a total of 13 evaluable patients will be accrued. If there are at least five FPRs among these 13 patients, the study will be considered a success, but will continue to accrue to 23 total patients to obtain further sufficient information about primary and secondary endpoints. Otherwise, it will move onto the second stage that will accrue an additional 10 evaluable patients. If there are two or fewer FPRs in the total of 23 subjects in the second stage, the trial will be stopped for futility. If there are ≥ 5 FPRs among these 23 patients, the study will be considered a success and accrual would end after the 23 total patients. Otherwise, ten additional evaluable patients will be accrued in the final third stage, resulting in a total sample size of 36. The null hypothesis will be rejected if there are ≥ 7 FPRs among these 36 subjects. Considering a dropout rate of 15%, approximately 43 subjects will be enrolled. If the true response rate is 7.9%, then the probability of stopping early for futility is 71.4%, the probability of stopping early for success is 4.4%, and the expected sample size is 26.2. When the trial is considered successful at the first or second interim analysis, a total of 23 evaluable patients will be accrued.

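### The look at 13 patients cannot change the trial's course: every result leads to 23 patients, and there is no futility stop at stage 1

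*Protocol article*

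**What the plan says.** The rules are in the protocol article, Statistical considerations, Sample size and interim analyses.

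- **Stage 1.** Thirteen evaluable patients. The success bound is five FPRs, and once it is met "the study will be considered a success, but will continue to accrue to 23 total patients". The stated purpose is to learn more on the endpoints. With four or fewer FPRs the trial goes on to stage 2, which adds ten evaluable patients.
- **Stage 2.** "If there are two or fewer FPRs in the total of 23 subjects in the second stage, the trial will be stopped for futility". Five or more of 23 is success and accrual ends. Three or four of 23 leads to stage 3.
- **Stage 3.** The null is rejected with seven or more FPRs among 36.

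The section closes by confirming that 23 evaluable patients are accrued after success at either interim. It gives a reason for continuing after early success, but says nothing on why there is no futility rule at 13.

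The stage 3 size is stated in two ways. The Study design section gives 13, which fits the total of 36. The Sample size section says ten.

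**The concern.** An interim look earns its place if some result at that look changes what happens next. Here none does. Success at 13 does not end accrual, and it cannot be reversed at 23 because responses only accumulate. Failure at 13, even with no response at all, does not end accrual either. The look can affect only when success may be announced.

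What is at stake is efficiency and patient exposure, not error control. If the escalated regimen does not raise the FPR rate, the first point at which the plan can act on that is 23 patients, although a reader of a three-stage design would expect a decision at 13. The ten patients in between also undergo the habitat biopsies and the escalated plan.

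**Working it through.** **Inputs** (Study design; Sample size and interim analyses): null FPR p0 = 7.9%, alternative p1 = 24%, stage sizes 13, 10 and 13, success bounds 5/13, 5/23 and 7/36, futility bound 2/23. The article states "one-sided significance level of 5% and a power of 81.8% if the true FPR is 24"%, and an expected sample size under the null of 26.2.

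**1. What each stage-1 result does.** Let X13 and X23 be the FPR counts at 13 and 23 patients.
- X13 = 0 to 4: continue to 23.
- X13 = 5 to 13: continue to 23. Since X23 ≥ X13, X23 ≥ 5 is certain.

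The verdict and the sample size therefore depend only on X23 and, when X23 is 3 or 4, on the last 13 patients.

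**2. Operating characteristics as written.**

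P(reject) = P(X23 ≥ 5) + P(X23 = 3)·P(Y ≥ 4) + P(X23 = 4)·P(Y ≥ 3), with Y binomial on 13 patients.

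E(N) = 23 + 13·P(X23 = 3 or 4).

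| | p = 7.9% | p = 24% |
|---|---|---|
| P(X23 ≤ 2) | 0.7283 | 0.0608 |
| P(X23 = 3) | 0.1684 | 0.1012 |
| P(X23 = 4) | 0.0722 | 0.1598 |
| P(X23 ≥ 5) | 0.0311 | 0.6783 |
| P(Y ≥ 4) | 0.0156 | 0.3822 |
| P(Y ≥ 3) | 0.0775 | 0.6364 |
| P(reject) | **0.0393** | **0.8186** |
| E(N) | **26.13** | **26.39** |

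The stated power reproduces (81.86% against 81.8%), type I error is within 5%, and the expected sample size is close to the stated 26.2. None of these expressions contains X13. Exact enumeration with the stage-1 look in place gives the same values.

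**3. Where the stage-1 bounds come from.** Fleming's formula with N = 36, p0 = 0.079 and z = 1.645 gives raw acceptance points of −0.83 at 13 patients and 1.93 at 23. The first cannot be reached and the second rounds to 2. The rejection points are 5, 5 and 7. These are the bounds in the article.

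**4. What happens after 0/13.**
- p = 7.9%: P(0/13) = 0.921^13 = 0.343. Given 0/13, the trial stops for futility at 23 with probability 0.961 and ends in rejection with probability 0.0015.
- p = 24%: P(0/13) = 0.76^13 = 0.028. Given 0/13, it ends in rejection with probability 0.245.

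**5. Adding a stop at 0/13, all else unchanged, 13 patients in stage 3.**
- Power: 0.8186 − 0.0282 × 0.2453 = 0.8117.
- Type I error: 0.0393 − 0.3431 × 0.0015 = 0.0388.
- Null saving: ten patients in 34.3% of trials (3.43), plus 13 patients in the share no longer reaching stage 3, 0.2406 − 0.2275 = 0.0131 (0.17). Total 3.60, so E(N) = 26.13 − 3.60 = 22.53.
- For comparison, stopping at one or fewer of 13 gives a null E(N) of 17.8 but power of 75.8%.

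**6. Effect of endpoint delay.** FPR is read at surgery, 3 to 12 weeks after radiotherapy (Radiological and pathological treatment evaluation). Assuming five fractions a week, 25 fractions take five weeks, so the result arrives 8 to 17 weeks after the start of radiotherapy. At 2 to 3 patients a month (Study design), about 4 to 12 more patients enter meanwhile unless accrual pauses. With four entered, the null saving is 0.343 × 6 + 0.17 = 2.2. With ten or more it is 0.17.

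**The case against.** The strongest reply is that nothing here is an error. The bounds are what the named Fleming design yields at these inputs, including the absence of a reachable futility point at 13. Power and type I error hold. Continuing after early success is stated openly, with a reason. All of this stands. The reason, however, covers only the success side, and continuing removes the one action that the formula left to stage 1.

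A reader might infer that ten more patients will receive an ineffective treatment. The documents do not support that as a fact. It is conditional on the escalation not working, and at a true rate of 24% a trial can still open with 0/13 and succeed. Nor do they support a claim that patients lose standard care, since the plan gives the rest of the tumor the standard 50 Gy and resection follows. FPR is an efficacy endpoint, and adverse events are assessed separately.

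Two practical objections also stand. The saving depends on pausing accrual, which the article does not mention. And recruitment began in March 2022, stage 1 was projected to take 6 months, and the protocol version is dated May 2023, so on the plan's own timetable stage 1 may already be enrolled. Actual accrual is not shown. A futility rule written after the stage-1 results are known would not be a prespecified one.

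**Conclusion.** The point holds as a design weakness that is cheap to improve, not as a mistake in the calculations. As written, the 13-patient look changes no sample size, error rate or conclusion. What is lost is the chance to stop early under the null after 0/13, worth up to 3.6 evaluable patients on average at a cost of 0.7 points of power.

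Three assumptions carry these figures: a true FPR of 7.9% for the saving; accrual held until the 13th patient's surgical pathology is known; and 13 patients in stage 3. If stage 3 has ten, power is already 77.0% before any change, so a claim that power stays above 80% depends on settling that first.

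The stated null probabilities of early stopping (71.4% futility, 4.4% success) also differ from the exact 72.8% and 3.1%. That is a separate matter and does not affect this conclusion.

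**What to change.** If stage 1 has not read out:

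- Add a rule that accrual stops for futility if there are no FPRs among the first 13 evaluable patients, and keep the other boundaries.
- State the stage 3 size as 13 in both sections, in line with the total of 36.
- Restate power as 81.2% and the null expected sample size as 22.5. Type I error stays at 3.9%.
- Say whether accrual pauses for the 13th patient's pathology. Without a pause, do not quote 22.5; give the smaller saving.

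The cost is a short amendment, 0.7 points of power and, if chosen, a pause of some weeks.

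If stage 1 has already read out, leave the boundaries alone. Describe the design as two-stage (23/36) and the 13-patient look as non-operative, and still reconcile the stage 3 size. This costs wording only.

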**Fig. 1 Fig1:**
[figure not shown]
Trial schema. Radiation therapy begins between visit 1 and visit 2. All patients will be seen during weekly treatment visits throughout radiation therapy. Radiation therapy ends between visit 2 and visit 3. Surgical resection occurs between visit 3 and visit 4

We hypothesize that GARD-optimized RT dose for STS (60 to 70 Gy in 25 fractions), delivered to MRI defined radiomic habitats will triple the FPR rate as defined by response in the surgical specimen of ≥ 95% cellular response. With 36 evaluable patients, this study has 81.8% power to detect an increase in the FPR rate from 7.9% (benchmark selected based on historical data) to 24%, with a one-sided alpha = 0.05. A Z-test with continuity correction will be used to determine changes in the FPR. Assuming 15% of patients will be unevaluable, up to 43 patients will be enrolled within 24 months. This trial uses Fleming’s 3-stage design, in which stage 1 accrual is 13 evaluable patients over 6 months, with a projected accrual rate of 2 patients per month. Stage 2 accrual is 10 and the final stage accrual is 13. Assuming 50% of the eligible patients over a 12-month period enroll in this trial, 3 patients per month will enroll.

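### Stage 3 is given as ten patients in one section and 13 in another; 23 + 10 is 33, not 36, and with ten the stated 81.8% power is not delivered

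*Protocol article*

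**What the plan says.** Two sections of the Protocol article describe the same three-stage design.

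- **Sample size and interim analyses.** Stage 1: "In the first stage, a total of 13 evaluable patients will be accrued". Stage 2 adds 10, for 23 in total. Stage 3: "ten additional evaluable patients will be accrued in the final third stage, resulting in a total sample size of 36". The null hypothesis is rejected at the end with at least 7 FPRs among 36. With 15% dropout, about 43 are to be enrolled. The design is described as one "which has a one-sided significance level of 5% and a power of 81.8% if the true FPR is 24"%.
- **Study design** (the paragraph after the Fig. 1 legend). Stage 1 is again 13 evaluable patients, and then: "Stage 2 accrual is 10 and the final stage accrual is 13". The power is tied to the total: "With 36 evaluable patients, this study has 81.8% power to detect an increase in the FPR rate from 7.9"% to 24%.

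The interim rules appear only in Sample size and interim analyses. At stage 1, "If there are at least five FPRs among these 13 patients, the study will be considered a success", with accrual continuing to 23. At 23 patients, two or fewer FPRs stops the trial for futility and five or more is a success. Stage 3 therefore opens only with 3 or 4 FPRs among 23. No futility bound is given for stage 1.

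**The concern.** The two sections disagree on the size of stage 3, and the decision-rule paragraph also disagrees with its own total. In a sequential design the last stage size and the final critical count are set together: a bound of 7 chosen for 36 patients is stricter when applied to 33.

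If the stage size of ten were acted on, there would be three ways forward at 33 patients: keep the bound of 7 and lose power, lower the bound, or extend accrual. The second and third would be unplanned changes made after outcomes had been seen. The primary analysis of a single-arm trial should not be left open to that choice.

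**Working it through.** **Inputs** (all from Sample size and interim analyses, except the second stage 3 size)

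- Null rate p0 = 0.079; alternative rate p1 = 0.24; one-sided 5%; stated power 81.8%.
- Stage 1: n = 13, success at ≥5. Stage 2: 10 more (23 in total), futility at ≤2, success at ≥5.
- Stage 3: 10 (Sample size and interim analyses) or 13 (Study design). Final rejection at ≥7.
- Dropout 15%, enrolment 43; stated expected sample size under p0, 26.2.

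**Step 1. The totals.** 13 + 10 + 10 = 33. 13 + 10 + 13 = 36.

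**Step 2. State of the trial at 23 patients.** Exact binomial probabilities, where a stage 1 success is counted as a success and is not re-tested at 23:

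| | p = 0.24 | p = 0.079 |
|---|---|---|
| Success at stage 1 (≥5/13) | 0.1816 | 0.0023 |
| Success at stage 2 (≥5/23) | 0.4967 | 0.0288 |
| Futility (≤2/23) | 0.0608 | 0.7283 |
| Continue with 3 FPRs | 0.1012 | 0.1684 |
| Continue with 4 FPRs | 0.1598 | 0.0722 |

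These do not depend on the size of stage 3.

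**Step 3. Final stage.** With n3 patients in stage 3, X ~ Binomial(n3, p) and final bound r:

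P(reject) = P(stage 1 success) + P(stage 2 success) + P(3 FPRs)·P(X ≥ r − 3) + P(4 FPRs)·P(X ≥ r − 4)

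*The plan's own figure first: n3 = 13, r = 7 (7 of 36).*

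- Power: 0.1816 + 0.4967 + 0.1012 × 0.3822 + 0.1598 × 0.6364 = 0.6783 + 0.1404 = **0.8186** (stated 0.818).
- Type I error: 0.0023 + 0.0288 + 0.1684 × 0.0156 + 0.0722 × 0.0775 = 0.0311 + 0.0082 = **0.0393**, within 5%.

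*n3 = 10, r = 7 (7 of 33).*

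- Power: 0.6783 + 0.1012 × 0.2012 + 0.1598 × 0.4442 = 0.6783 + 0.0913 = **0.7696**.
- Type I error: 0.0311 + 0.1684 × 0.0055 + 0.0722 × 0.0388 = 0.0311 + 0.0037 = **0.0348**.

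*n3 = 10, r = 6 (6 of 33).*

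- Power: 0.6783 + 0.1012 × 0.4442 + 0.1598 × 0.7327 = 0.6783 + 0.1620 = **0.8403**.
- Type I error: 0.0311 + 0.1684 × 0.0388 + 0.0722 × 0.1842 = 0.0311 + 0.0198 = **0.0509**, above 5%.

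So with ten patients, a bound of 7 misses the stated power and a bound of 6 exceeds the stated significance level.

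**Step 4. Cross-checks against other stated figures.**

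- Enrolment: 36/0.85 = 42.4, rounded up to 43 as stated. 33/0.85 = 38.8, rounded up to 39.
- Expected sample size under p0, with 23 evaluable patients accrued in every case. The plan's own stopping probabilities (71.4% futility, 4.4% success) leave 24.2% to continue. With 13: 23 + 13 × 0.242 = 26.1. With 10: 23 + 10 × 0.242 = 25.4. The stated value is 26.2.

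The total, final bound, power, enrolment and expected sample size all go with 13.

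**The case against.** The case for treating this as minor is that the design itself is intact. The 81.8% is tied to 36 evaluable patients and reproduces at 36. The sentence containing the slip gives 36 as the total, the next applies the final test to 36, the enrolment of 43 follows from 36, and Study design lists 13, 10 and 13. To stop at 33, a team would have to follow one word and overlook the rest. Nowhere does the article state a total of 33 or a bound of 6 of 33. Stage 3 is reached only about 24% of the time at a true rate of 7.9% and 26% at 24%, and with the bound of 7 kept the type I error would fall, not rise. Finally, this is an article condensing protocol version 1.4, which is not shown and may have the correct figure.

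Most of this stands, and it limits the finding: no power defect exists in a 36-patient trial, and the 77.0% arises only if ten is acted on. What does not stand is that the slip can be left. It concerns a stage size in the only full statement of the decision rules, and a reader has to cross-check another section to recover the design. Whether the full protocol has the same error cannot be told from the article, which is a reason to check it.

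**Conclusion.** The concern holds. The decision-rule paragraph contradicts both its own total and Study design on the size of stage 3, and the article's other figures show that 13 is the intended number. If ten were followed with the bound of 7 kept, power at 24% would fall from 81.9% to 77.0%, a loss of 4.9 percentage points, and type I error would go from 3.9% to 3.5%. Lowering the bound to 6 does not rescue the ten-patient version, because type I error becomes 5.1%.

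These figures assume exact binomial probabilities, the bounds as stated, no futility stop at stage 1, and a stage 1 success counted as final even though accrual continues to 23.

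One related difference does not affect this point: the stated early-stopping probabilities at 7.9% (71.4% futility, 4.4% success) are not what the stated bounds give (72.8% and 3.1%), although the expected sample size is close (26.1 against 26.2).

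**What to change.** In Sample size and interim analyses, change the stage 3 accrual from ten to 13 additional evaluable patients. Keep the total of 36, the final bound of at least 7 of 36, and the enrolment of 43. Check the full protocol (version 1.4) for the same wording and correct it there if it occurs, before stage 3 accrual begins. This is a one-word correction: it needs no new calculation and no change to the planned sample size or the decision bounds.

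### The quoted null probabilities of early stopping (71.4% futility, 4.4% success) do not follow from the stated boundaries, which give 72.8% and 3.1%

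*Protocol article*

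**What the plan says.** All of this is in the protocol article under the heading Sample size and interim analyses.

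- Null value: "The null hypothesis that the true FPR is 7.9" percent.
- Alternative: the null is "tested against a 1-sided alternative hypothesis that the FPR is 24" percent.
- Level and power: Fleming's three-stage design, "which has a one-sided significance level of 5% and a power of 81.8% if the true FPR is 24" percent.
- Stage 1 size: "In the first stage, a total of 13 evaluable patients will be accrued".
- Stage 1 limit, for success only and with no futility rule at this look: "If there are at least five FPRs among these 13 patients, the study will be considered a success". Accrual nevertheless goes on to 23.
- Stage 2 size, when the stage 1 limit is not met: "it will move onto the second stage that will accrue an additional 10 evaluable patients".
- Stage 2 limits, judged on all 23 patients: five or more FPRs is a success, and the lower limit reads "If there are two or fewer FPRs in the total of 23 subjects in the second stage, the trial will be stopped for futility".
- Stage 3: the null is rejected with seven or more FPRs in 36.
- Behaviour at a true rate of 7.9%: "the probability of stopping early for futility is 71.4%, the probability of stopping early for success is 4.4" percent, with an expected sample size of 26.2.

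**The concern.** The paragraph specifies the decision rule completely, so its stopping probabilities under the null are fixed by arithmetic. The two that are printed differ from the exact values by 1.3 to 1.4 percentage points, although they are given to one decimal.

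The early-success figure also fails a consistency check. Early false success is one part of the total type I error and cannot exceed it, yet 4.4% is larger than the exact total for these boundaries (3.9%).

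Beyond the nominal 5%, this sentence is the article's only account of how the design behaves when the treatment adds nothing. A reader relying on it would misjudge the chance of a false claim of success at an interim look. A reader trying to reproduce the design could not tell whether the boundaries or the probabilities are wrong.

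**Working it through.** **Inputs** (from Sample size and interim analyses unless noted)

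- Null rate 0.079; alternative rate 0.24.
- Looks at 13, 23 and 36 evaluable patients.
- Success at ≥5 of 13 or ≥5 of 23; futility at ≤2 of 23; final rejection at ≥7 of 36.
- Stage 3 size 13. The paragraph says ten more patients, but its total of 36 after 23 requires 13, and the Study design section also gives 13.

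**Reduction of the rule.** Five FPRs by patient 13 means at least five by patient 23. With X the number of FPRs in 23 patients:

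- P(futility) = P(X ≤ 2)
- P(early success) = P(X ≥ 5)
- P(go to stage 3) = P(X = 3) + P(X = 4)
- P(reject at stage 3) = P(X = 3)·P(Y ≥ 4) + P(X = 4)·P(Y ≥ 3), where Y is the number of FPRs in the 13 stage 3 patients

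**Step 1: reproduce the stated power (rate 0.24)**

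- P(X ≥ 5) = 0.6783 and P(X ≤ 2) = 0.0608
- Stage 3 rejection = 0.1012 × 0.3822 + 0.1598 × 0.6364 = 0.0387 + 0.1017 = 0.1404
- Power = 0.6783 + 0.1404 = 0.8186

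The article states 81.8%, so the boundaries have been read as intended.

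**Step 2: the same rule at the null (rate 0.079)**

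- P(X = 0), P(X = 1), P(X = 2) = 0.1507, 0.2972, 0.2804, so P(futility) = **0.7283**
- P(X ≥ 5) = **0.0311**, of which 0.0023 arises at stage 1 and 0.0288 at stage 2
- P(go to stage 3) = 0.1684 + 0.0722 = 0.2406
- Stage 3 rejection = 0.1684 × 0.0156 + 0.0722 × 0.0775 = 0.0026 + 0.0056 = 0.0082
- Total type I error = 0.0311 + 0.0082 = **0.0393**
- Expected N = 23 + 13 × 0.2406 = **26.1**, since accrual runs to 23 even after a stage 1 success

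| At 7.9% | Stated | Exact |
|---|---|---|
| Early futility | 71.4% | 72.8% |
| Early success | 4.4% | 3.1% |
| Expected N | 26.2 | 26.1 |
| Total type I error | nominal 5% | 3.9% |

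**Step 3: can another reading rescue the figures?**

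- Null rate of 8.0%: 72.2% and 3.3%.
- Solving for the rate under the stated boundaries: 71.4% futility needs 8.12%, while 4.4% early success needs 8.67%. No single rate gives both.
- Poisson approximation: 72.6% and 3.8%.
- Normal approximation with continuity correction: 70.1% and 1.9%.
- Stage 1 success limit of 4 instead of 5: 72.8% and 3.7%.
- Stage 3 of ten patients: no effect, because both probabilities are settled at patient 23.

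**The case against.** The strongest counter-argument is that almost nothing depends on these figures. The stated probabilities imply a total chance of early stopping of 71.4 + 4.4 = 75.8%; the exact value is 72.8 + 3.1 = 75.9%. Power, level and expected sample size all survive, and the stated early-success figure errs towards overstating the false-positive risk. This is correct, and it limits the weight of the point. It does not make the printed figures right.

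Second, 4.4% is below the nominal 5%, so the article does not contradict its own stated level. That also stands: the impossibility is relative to the exact 3.9%. Adding 4.4% to the 0.8% from stage 3 gives 5.2%, an apparent breach of the level, but that sum mixes a stated with a recomputed number and should carry little weight.

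Third, the figures may have a simple origin. At a true rate of about 8.12% the same rule gives futility 71.4% and a total rejection probability of 4.4%, with expected N of about 26.2 to 26.3. The 4.4% could then be the overall type I error at a slightly different null rate, printed under the wrong label. This is inference; nothing in the article confirms it. It is a good reason to check the design output before replacing numbers, but even if true it leaves the sentence wrong at its stated 7.9%.

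Fourth, the total error, expected N and power above assume 13 patients in stage 3. That assumption is forced by the total of 36, and the two disputed probabilities do not use it.

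**Conclusion.** The concern holds. With the stated boundaries and a true rate of 7.9%, early futility stopping has probability 72.8% rather than 71.4%, and early success 3.1% rather than 4.4%. The early-success figure is too high by 1.3 percentage points, about 40% in relative terms (4.4/3.1 = 1.42). The exact overall type I error is 3.9%.

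The result rests on exact binomial enumeration of the written rule with independent patients. The two disputed probabilities need no other assumption; the total error, expected N and power also take stage 3 as 13 patients. The practical effect is modest: the rule keeps its 5% level, the power reproduces, and no boundary or sample size needs to change. What is wrong is the description of the design's behaviour under the null.

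**What to change.** Check the design software output for the null rate and boundaries actually used. If they are those printed, replace the null figures with: futility 72.8%, early success 3.1%, overall type I error 3.9%, expected evaluable sample size 26.1. If the output used another null rate or other boundaries, print those, so that rule and probabilities agree; if 4.4% proves to be the overall type I error, label it so.

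In the same edit, reconcile the stage 3 size: the paragraph says ten, whereas its total of 36 and the Study design section require 13. With ten, power would fall to 77.0%.

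It would also help, though it is not needed to correct the error, to give the matching figures at 24%: power 81.9%, futility 6.1%, early success 67.8%.

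The cost is a few numbers in one paragraph, with no change to the design, the accrual or the analysis.
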